#### Participants and the Randomized Control Process

Eligible adolescents in grades 7-8 and their parents will be recruited from 8 secondary schools through cluster-randomized sampling. The inclusion criteria for adolescent participants will include (1) aged between 11-16 years (inclusive) with 1 parent willing to participate; (2) Chinese youths who can read and write in Chinese language; (3) sufficient visual and auditory abilities to complete the intervention and assessment; and (4) ability to give consent to participate in the study. Exclusion criteria for adolescent participants will include (1) no parental consent; (2) inability to remain focused to complete the intervention and the survey, which take approximately 45 and 25 minutes respectively; and (3) intellectual disability or severe illness or pain that would lead to significant bias in students’ health and mental health situation.

Inclusion criteria for parent participants are (1) living with the child participant; (2) Chinese-language proficiency and comfort with completing computer-based activities; (3) sufficient visual and auditory abilities to complete the intervention and assessment; and (4) ownership of personal internet-equipped devices. Exclusion criteria for parent participants include (1) having a mental illness as well as exclusion criteria (2) and (3) from the aforementioned criteria for adolescent participants.

The school and student recruitment process will include the following steps. First, we will send research invitations to schools chosen randomly from the secondary school list covering 3 areas of Hong Kong (ie, Hong Kong Island, Kowloon, and the New Territory). Invitations will not stop until 8 schools agree to participate. Then, 3 classes from grades 7 or 8 will be selected by a random number, and all students in the selected class will be invited to join the study. There are generally 35 students in 1 class. We estimate that approximately 25 pairs of parents and students will join the study. If too few participants join the study, the random class selection process will be repeated until 70 pairs of eligible parent-child participants in each school are recruited. Using random numbers, the selected 3 classes will be assigned to the PC-SMILE intervention group, the C-SMILE intervention group, and the waitlist control group. If the targeted sample size is met, the school invitation and recruitment will stop.

Students and parents will complete all study procedures via personal internet-equipped devices. Parent-student pairs will be assigned to the same condition (the PC-SMILE or C-SMILE or waitlist). They will receive the link of research material and complete Qualtrics-based baseline survey, intervention, and follow-up surveys independently. For student participants, the interventions will be conducted in school classrooms or activity rooms that offer sufficient computers or tablets, and headphones. All intervention activities will be self-administered by youths and delivered in a web-based format. The research team and trained research assistants will remain in the intervention rooms to provide help if needed. Parent participants will receive a study link with the baseline Qualtrics survey and the intervention. The interventions for parents and students are different in terms of narrative and content. Between the 2-week posttest and the 3-month follow-up survey, a total of 5 weekly booster messages with core intervention content will be sent to the intervention groups every 2 weeks. After completion of the 3-month follow-up, parents in the C-SMILE or the control group who do not initially receive the intervention will be granted the intervention access.

### Intervention Groups

#### PC-SMILE Group

The PC-SMILE integrates the growth mindsets of intelligence, failure, and negative emotions and introduces these growth mindsets to students and parents. The interventions for both students and parents consist of five components: (1) an introduction to brain functions regarding the potential of neuroplasticity and the possibility of changes in intelligence and emotions, (2) stories and testimonials from school-aged youths who describe their belief-in-change, (3) short videos with stories of improving intelligence and emotions and of failure-is-enhancing, (4) common questions and misconceptions about growth mindset, and (5) self-persuasion writing exercises in which the participants write notes to young students or others about the growth mindsets. The interventions for parents and students are different in terms of narrative and content. Between the 2-week posttest and the 3-month follow-up survey, a total of 5 weekly booster messages with core intervention content will be sent to the intervention groups every 2 weeks. The interventions for children and parents last 45 minutes.

#### C-SMILE Group

In the C-SMILE group, only students receive the child-version intervention, but their parents do not receive parent-version intervention until the 3-month follow-up is finished. Parents are invited to do the preintervention survey and the 3-month follow-up survey.

### Waitlist Control Group

The waitlist control group will continue with normal education activities and do the preintervention and follow-up surveys at the same timeframe as the intervention groups. Participants and their parents in the waitlist group will be invited to complete the PC-SMILE after the 3-month follow-up survey.

### Measurements

Participants will be invited to read the instructions of the survey and complete self-rated scales. All the measures have been pilot-tested, and the questionnaires take approximately 25 minutes to complete.

Mindset about intelligence will be measured using the 3-item Implicit Theory of Intelligence Scale, which measures beliefs about the malleability of intelligence (eg, “You have a certain amount of intelligence and there is really not much you can do to change it”) [41,42]. Each item is rated on a 6-point scale (1=strongly disagree to 6=strongly agree). A higher score represents a more fixed mindset. The Cronbach α in the previous study was 0.87 with good validity [42,43].

Mindset about failure will be measured by the 6-item Implicit Theory of Failure Scale [16], which measures views of failure as enhancing versus debilitating on a 6-point Likert scale (1=strongly disagree to 6=strongly agree). A sample item of an enhancing belief is “The effects of failure are positive and should be used,” and a sample item of a debilitating belief is “The effects of failure are negative and should be avoided*.*” Enhancing belief items will be reverse scored. A higher score reflects more debilitating beliefs. The Cronbach α of the parent survey in the previous study was 0.88 [16].

Mindset about emotion will be assessed using the validated Chinese version of the 12-item Mindset of Depression, Anxiety, and Stress Scale [35] to measure children’s belief in the change of negative emotion states. Sample items include “When you have a certain level of depression/anxiety/stress, you really cannot do much to change it.” Parents’ mindset about emotion will be measured by a 4-item version of Mindset of Depression, Anxiety, and Stress Scale, which includes sample item “If they want to, people can change the emotions they have.” Each item is scored on a 6-point Likert scale (1=strongly disagree to 6=strongly agree), and a higher score means a more fixed mindset (Cronbach α=0.94) [35].

### Primary Outcome

Children’s depression and anxiety symptoms will be measured using the validated 25-item Revised Children’s Anxiety and Depression Scale for both children and parents [44,45]. Sample items measuring anxiety and depression include “I/My child worry when I/My child think I/My child have done poorly at something” and “‘I/My child feel sad or empty.” The frequency of each item is rated on a 4-point Likert scale with reference to the past 2 weeks (0=never to 3=always). The child survey has an overall score, total anxiety score from the anxiety subscale (Cronbach α=0.94), and total depression score from the depression subscale (Cronbach α=0.79) [44].

### Secondary Outcomes

The 4-item Hopelessness Scale [46,47] will be used to measure children and parents’ faith in the future. Each item is scored on a 5-point Likert scale from 1=strongly disagree to 5=strongly agree, and the mean of all 4 items is taken to measure hopelessness, with a higher score corresponding to a higher level of hopelessness. An example item is “My future seems dark to me.” The Cronbach α was 0.834 with good validity [48].

The validated Chinese version of Short Warwick-Edinburgh Mental Well-Being Scale [49,50] will be used to measure children’s and parents’ general experience of well-being. The Short Warwick-Edinburgh Mental Well-Being Scale includes 7 items scored on a 5-point Likert scale from 1=none of the time to 5=all the time, and the average of all 7 items indicates participants’ well-being. A higher averaged score represents a higher level of well-being. A sample item is “I have been feeling optimistic about the future.” The Cronbach α was 0.93 [50].

Parent-child interactions will be assessed by 3 self-developed questions about how many days the children spend more than 15 minutes per day doing activities with their parents in a week. Children will answer the frequency by the number of days from 0=none to 7=seven days. Parenting activities include chatting, handing out, and watching television or movies or videos. Student participants who rate higher frequency of the parenting activities have better interactions with parents. Parent-child relationships will be measured using 3 self-developed items. Questions are “I am very satisfied with the relationship between me and my parents,” “I proactively tell my family what had happened to me,” and “I proactively share my feelings with my family” for adolescents. The adapted items “My children are very satisfied with the relationship between them and their parents,” “My children proactively tell me what had happened to them,” and “My children proactively share their feelings with me” are for parents. Each item is rated on a 4-point Likert scale (1=strongly disagree to 4=strongly agree). A higher score indicates a better parent-child relationship.

Perceived parent learning versus performance orientation will be assessed from both children and parents’ perspectives. Child-version has 8 items and parent-version has 12 items, with half of the items measuring performance-orientation and half measuring learning orientation mindset, respectively [16]. The scale asks participants about the parents’ responses to a scenario when their child gets a poor grade on a quiz. Sample items of performance-orientation are “My parents don’t like it when I make mistakes in school” (child-version) and “I might worry (at least for a moment) that my child isn't good at this subject” (parent-version). Sample items of learning-orientation are “My parents want me to understand school concepts, not just do the work” (child-version) and “I’d discuss with my child whether it would be useful to ask the teacher for help” (parent-version). Participants rate the items on a 6-point Likert scale (1=strongly disagree to 6=strongly agree), and higher scores on performance- or learning-orientation items indicate their preferred orientations. The Cronbach α in previous study were 0.79 and 0.78 for performance-orientation and learning-orientation, respectively [16].

Academic self-efficacy will be measured by a 5-item scale that was adapted from the part of Patterns of Adaptive Learning Survey [51]. Children will rate the extent to which the skills taught in class could be mastered and the work could be done on a 6-point Likert scale (1=strongly disagree to 6=strongly agree). The sample question is “I’m certain I can master the skills taught in class.” A higher score means a higher level of academic self-efficacy.

The motivation for applying the contents learned from the intervention will be assessed right after the intervention. We will ask participants the extent to which they would like to apply the intervention contents in life, and the extent to which they would like to improve their ability to cope with challenges on a 6-point Likert scale from 1=not very likely to 6=very likely.

The intervention feedback scale will be used to assess the acceptability of parent and child interventions. The scale will ask parents and children to indicate how much they enjoyed, understood, and felt helped by the program; whether they would recommend the program to a friend; whether they found the program interesting and fun; whether they agree with the program’s message; whether the program is a burden; and the overall acceptability regarding this program [26]. Participants rate the items on s 5-point Likert scale (1=strongly disagree to 5=strongly agree). The items will be analyzed collectively as a single item.

### Covariates

Sociodemographic information will be collected from parents and will cover a range of participant characteristics (gender, age, grade, and socioeconomic status) at baseline to examine variability between the groups.

### Data Analysis

An intention-to-treat approach will be adopted. A 2-level analysis will be used to account for the cluster randomization [52]. To examine the effects of the interventions, multilevel regression will be used to test the group effect, time effect, and interaction effect on outcome measures. Additionally, we will calculate effect sizes using estimated marginal means; these effect sizes compare mean change scores (Cohen *d*), reflecting the standardized levels of change in each outcome from baseline to 2 follow-ups for youths receiving the mindset versus active control interventions. A 95% CI will be provided for each effect size. SPSS (version 26; IBM Corp) will be used for all statistical analysis.

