**Methods:**

A total of 549 parent-child dyads will be recruited from 8 secondary schools and randomly assigned to either the PC-SMILE intervention group, the C-SMILE intervention group, or the no-intervention waitlist control group. The 45-minute interventions include parent-version and child-version. Both parents and students in the PC-SMILE group receive the intervention. Students in C-SMILE group receive intervention and their parents will receive intervention after all follow-up ends. Students in 3 groups will be assessed at 3 time points, baseline before intervention, 2 weeks post intervention, and 3 months post intervention, and parents will be assessed in baseline and 3-month follow-up. The intention-to-treat principle and linear-regression-based maximum likelihood multilevel models will be used for data analysis.

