### Research Design

This study will be a 3-arm cluster-RCT with a waitlist control group design. A conceptual model is provided in Figure 1. The intervention protocol will strictly follow the CONSORT (Consolidated Standards of Reporting Trials) guidelines [39,40] and has been preregistered before data collection in Open Science Framework and ClinicalTrials.gov. Classes in each eligible school will be randomized (using computer-generated random numbers) into the PC-SMILE intervention, C-SMILE, or waitlist group. The waitlist group will undergo intervention after the 3-month postintervention survey. All student participants will receive regular educational activities and interventions in school. A total of 3 repeated assessments of the measures will be conducted simultaneously for the children in three groups at (1) baseline, (2) 2-weeks post intervention, and (3) 3-months post intervention (Multimedia Appendix 1). The CONSORT flow diagram is provided in Figure 2. Cluster randomization will be conducted at the class level.

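### The two levels of the planned model are not named, and each plain two-level form gives a wrong standard error under plausible variance components, because the data are occasions within students within classes

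*Protocol article*

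**What the plan says.** The Data Analysis section commits to a number of levels and links it to the design: "A 2-level analysis will be used to account for the cluster randomization". It then says that "multilevel regression will be used to test the group effect, time effect, and interaction effect on outcome measures", and that effect sizes will compare change from baseline to the two follow-ups.

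The design is in other sections:
- **Occasions.** Research Design: "A total of 3 repeated assessments of the measures will be conducted simultaneously for the children in three groups".
- **Unit of randomisation.** Research Design: "Cluster randomization will be conducted at the class level".
- **Block.** Research Design: "Classes in each eligible school will be randomized". The section on participants and randomisation adds: "Using random numbers, the selected 3 classes will be assigned to the PC-SMILE intervention group, the C-SMILE intervention group, and the waitlist control group". Each school therefore supplies one class per arm.

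The abstract gives the estimator: "linear-regression-based maximum likelihood multilevel models will be used for data analysis". The article does not say what the two levels are, what covariance a student's three scores have, or whether school enters the model.

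**The concern.** Two kinds of dependence bear on the treatment comparison: scores from the same student are correlated, and students in the same class are correlated. A plain random-intercept model with two levels carries only one of them, and the consequence depends on which one is dropped.

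The Discussion names the 3-month follow-up as the primary outcome, and the effect sizes are changes from baseline. The group-by-time contrast therefore carries most of the primary inference, and its confidence intervals rest on the same variance model. An analyst who follows the text could fit a valid model, one that rejects too often, or one that rejects too seldom, and each would match the description.

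**Working it through.** **Inputs from the article.** 8 schools with 3 classes each give 24 classes, 8 per arm. This count is derived, and it may change because class selection can be repeated or recruitment stopped. With 549 pairs, m = 549/24 = 22.9 students per class. There are 3 occasions.

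The article's own sample size reproduces as an individually randomised two-group t-test: d = 0.33, 80% power and two-sided 0.05 give 145.1, so 146 per arm; 146/0.8 = 182.5, so 183; 183 × 3 = 549. That calculation supplies no ICC or other variance component to use here.

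**Assumed inputs.** Total variance 1; within-student correlation 0.6; class ICC (c) 0.01 to 0.05; class-by-time variance (k) 0 to 0.02; school variance 0.01 to 0.05.

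**Method.** The arms have equal numbers of classes, so the ratio of the model's SE to the true SE is the square root of (model variance / true variance) of a class mean or class-mean change. Type I error is 2Φ(−1.96 × ratio).

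**Reading A: observations within classes, no within-student covariance.** For group-by-time the model variance is 2(1 − c)/m. The true variance is 2k + 2(0.4 − k)/m. With c = 0.02:
- k = 0: 0.0857 against 0.0350; ratio 1.57; type I error 0.002.
- k = 0.02: 0.0857 against 0.0732; ratio 1.08; type I error 0.034.

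In a balanced design the group main effect is still judged against class-level variance. In a separate simulation (24 classes of 18, student share 0.58), power for d = 0.33 under this reading was about 53 to 54%, against 56 to 84% for a correct change analysis. The gap is largest when class-by-time variance is small and nearly closes at the upper end.

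**Reading B: occasions within students, class ignored.** For the group effect the model variance is (0.6 + 0.4/3)/m = 0.0321. The true variance is c + (0.6 − c)/m + 0.4/(3m).

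| c | true variance | SE ratio | type I error |
|---|---|---|---|
| 0.01 | 0.0416 | 0.88 | 0.085 |
| 0.02 | 0.0512 | 0.79 | 0.121 |
| 0.05 | 0.0799 | 0.63 | 0.214 |

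For group-by-time the model variance is 2(0.4)/m = 0.0350:

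| k | true variance | SE ratio | type I error |
|---|---|---|---|
| 0 | 0.0350 | 1.00 | 0.050 |
| 0.005 | 0.0445 | 0.89 | 0.082 |
| 0.01 | 0.0541 | 0.80 | 0.115 |
| 0.02 | 0.0732 | 0.69 | 0.176 |

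A simulation with 23 students per class and 20,000 runs per setting gave 0.114 and 0.177 for the last two rows, and 0.120 and 0.216 for the group effect at c = 0.02 and 0.05.

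**School left out.** For a level contrast the SE ratio is √[(school + v)/v], with v = c + (1 − c − school)/m. At c = 0.02 and school = 0.02, v = 0.0620, the ratio is 1.15 and type I error is 0.024. Over the assumed range the ratio is 1.05 to 1.41 and type I error 0.006 to 0.039, which is conservative throughout. A school intercept cancels from group-by-time.

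**Full ML.** With 24 class means and 3 arm means, the class-level SE is √(21/24) = 0.935 of its correct value. Type I error is about 0.065 with a t reference on 21 df and 0.081 with a normal reference.

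**Class-level error terms.** In the same simulation, a school-blocked class-level test on 14 df held 0.041 to 0.051 for the group effect at class ICC 0.02 to 0.05. A class-level change analysis on 21 df held 0.046 to 0.050 for group-by-time at k = 0.01 to 0.02. Both fall below nominal (0.024 and about 0.03) when the corresponding variance is zero.

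**The case against.** The strongest reply is that a two-level model can be correct. Students within classes with a random class effect, and the three occasions handled by a within-student residual covariance, is valid for the group effect and can fairly be called two-level. So is a single follow-up analysed with baseline as covariate. Nothing in the article rules these out. A reader might infer that two levels cannot fit this design, or that the standard errors are bound to be wrong. The article does not support either inference. What it does show is that neither valid form is specified.

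Second, the sentence ties the two levels to the cluster randomisation, so class is the natural upper level. That makes reading A more literal than reading B, and the likelier fault is lost power, not false positives. This stands. So does the point that with class ignored the group-by-time test is nominal if class-by-time variance is zero.

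Third, the article's silence on school is not a statement that school is excluded, and an article may leave block terms to a fuller plan. A reader might also expect that omitting the block inflates type I error. The working shows the opposite for level contrasts and no effect of a school intercept on group-by-time.

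Fourth, maximum likelihood appears only in the abstract, in a phrase that need not exclude REML. This keeps the ML point secondary.

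**Conclusion.** The point holds as a specification that does not match the design. The article fixes the number of levels without naming them, and both plain two-level readings give wrong standard errors under plausible variance components, in opposite directions. Under the more literal reading the group-by-time SE is about 1.1 to 1.6 times too large. Under the other reading, type I error is about 0.09 to 0.21 for the group effect and, only where class-by-time variance is about 0.005 to 0.02, about 0.08 to 0.18 for group-by-time.

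These sizes rest on an assumed within-student correlation of 0.6, the assumed class and class-by-time variances, and a derived count of 24 equal classes. The direction under each reading does not depend on the exact values, except that reading B's group-by-time error vanishes when class-by-time variance is zero. School is a matter of precision for level contrasts. Full ML, if that is what is meant, would make class-level SEs about 6 to 7% too small.

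**What to change.** In Data Analysis, replace the two-level wording with a mixed model that has:
- a student random effect, or an unstructured covariance across the three visits within student;
- a random class intercept and a class-by-visit term;
- school as a fixed block effect.

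The class-by-visit term matters: a third level with random intercepts alone would not correct the group-by-time test if a class-by-time component exists.

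As a secondary edit, state REML with Satterthwaite degrees of freedom and align the abstract. This should accompany the school term. With 8 school and 2 further arm parameters, 24 − 10 = 14 class-level df remain, and full ML would then shrink the class-level SE to √(14/24) = 0.76 of its correct value.

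The cost is analysis wording and a few lines of code. Compared with a model that ignores class, intervals may widen to their correct size. A small class-by-visit variance may be estimated at zero, and the plan should say what is done then. The Results section reports only one school enrolled so far, so the change can be made before most outcome data exist.

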#### Hypotheses

This study will examine the effectiveness of the PC-SMILE for adolescents and their parents by comparing it to a child single-session intervention on mindset of intelligence, failure, and emotion (C-SMILE) intervention group that provides the child-version intervention to children only and a no-intervention waitlist control group.

Our hypotheses are the following:

H1: The PC-SMILE and C-SMILE groups have better improved primary outcome compared to the waitlist control group, including reducing anxiety and depression symptoms in student participants, while PC-SMILE is more effective than C-SMILE.

H2: The PC-SMILE and C-SMILE are more effective in the secondary outcomes of (1) reducing hopelessness, (2) enhancing academic self-efficacy, (3) enhancing psychological well-being, and (4) enhancing parent-child interactions and relationships than waitlist control, and PC-SMILE is more effective than C-SMILE.

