Fourth, as in previous interventions [14,32], storytelling is a powerful feature of the PC-SMILE. Participants learn the stories from valued others, such as older peers and experts, which is helpful in conveying the core messages of the growth mindset. We also use the “saying-is-believing” exercise to invite the participants to share their learnings from the intervention with future intervention users. This exercise helps participants to internalize the growth mindset through cognitive dissonance processes [19,37].

Fifth, as the effects of SSIs may wane over time, booster messages will be adopted in the PC-SMILE. Weekly booster reminders [38] of core growth mindset quotations will be sent to both parent and child participants via email or text messages to sustain the mindset and behavioral changes.

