## Discussion

### Expected Findings

This study develops the first a parent-child single-session integrated mindset intervention for Chinese adolescents which simultaneously targets to promote the growth mindset of intelligence, failure, and emotion among adolescents and their parents. This RCT will provide empirical evidence on the effectiveness of the intervention. The hypothesized main finding would be that PC-SMILE intervention has better intervention outcomes, including decreased anxiety and depression symptoms, reduced hopelessness, enhanced academic self-efficacy, psychological well-being, and parent-child interactions and relationships, than child intervention only or a waitlist control group.

As one of the first few attempts on parental mindsets, we will compare the effectiveness of parent-child intervention and child intervention only. This will be the unique evidence to show if intervention targeting parental mindset helps improve children’s mental health outcome.

The challenge of SSIs is that it may be difficult to have sustainable and long-term effects. Thus, we measure the 2-week and 3-month follow-up with the latter as the primary outcome. This evidence-based program is novel, feasible and scalable to meet the needs of a large number of young people across the country. The digital delivery of PC-SMILE ensures that it has the potential to be scalable to provide consistent, evidence-based, and prevention-focused psychoeducation. However, given the scale of the study, a key limitation includes the reliance on self-report measures and lack of objective measurement. Although we measure parent-reported depression and anxiety symptoms and parent-child interaction time, the general mode of measure is self-report. Future directions would be incorporating objective measurements alongside self-report measures, such as behavioral observations in schools.

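### The 3-month follow-up is named as primary in the Discussion, but neither H1, the primary outcome section nor the Data Analysis section designates a 3-month contrast as the test

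*Protocol article*

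**What the plan says.** The primary time point appears once, in the Discussion under Expected Findings: "we measure the 2-week and 3-month follow-up with the latter as the primary outcome". The reason given there is that lasting effects may be hard to achieve with a single session. The PC-SMILE Intervention section shows the same worry: "as the effects of SSIs may wane over time, booster messages will be adopted".

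The sections that define the confirmatory question give no time point:

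- **Hypotheses (H1):** "The PC-SMILE and C-SMILE groups have better improved primary outcome compared to the waitlist control group", with PC-SMILE also expected to do better than C-SMILE.
- **Primary Outcome:** "Children’s depression and anxiety symptoms will be measured using the validated 25-item Revised Children’s Anxiety and Depression Scale".
- **Sample Size Determination:** d = 0.33, power 0.80, α .05, 146 per arm, with no visit attached to the effect size.
- **Data Analysis:** "multilevel regression will be used to test the group effect, time effect, and interaction effect on outcome measures". Cohen d values follow, "reflecting the standardized levels of change in each outcome from baseline to 2 follow-ups", each with a 95% CI.

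Students are assessed at baseline, 2 weeks and 3 months. For parents, the Abstract says "parents will be assessed in baseline and 3-month follow-up".

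**The concern.** The tests listed under Data Analysis are not tied to the time point that the authors call primary. A group effect averaged over all visits includes baseline, where randomised arms should not differ. A time effect says nothing about differences between arms. A joint arm-by-time interaction responds to a difference in change at either follow-up. None of these, read in that way, asks whether the arms differ at 3 months.

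The authors chose 3 months because benefit may fade. If a joint interaction, or whichever follow-up looks better, were taken as support for H1, a benefit that had gone by 3 months could be reported as a positive primary result. The issue concerns student-reported outcomes, since parents have only one follow-up.

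**Working it through.** **1. The plan's own sample size.** Inputs from Sample Size Determination: d = 0.33, power 0.80, α .05 (taken as two-sided). The normal formula gives n per arm = 2(1.960 + 0.842)² / 0.33² = 144.1, so 145. The t-based solution is 145.11, so 146 per arm and 438 in total. With 20% attrition, 146 / 0.80 = 182.5, so 183 per arm and 549 in total. The stated figures reproduce. They correspond to a two-arm comparison at a single time point, not to an arm-by-time test.

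**2. Joint interaction under a transient effect.** Assumptions not in the article:

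- time is categorical;
- SD is 1 at each visit, with equal correlation ρ between any two visits of the same child;
- the effect is d = 0.33 at 2 weeks in both active arms and exactly zero at 3 months.

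The two changes from baseline have covariance S = (1 − ρ)[[2, 1], [1, 2]], with inverse [[2, −1], [−1, 2]] / (3(1 − ρ)).

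The mean changes at 2 weeks are 0 (waitlist), 0.33 and 0.33, with overall mean 0.22. The squared deviations sum to 0.22² + 2 × 0.11² = 0.0726. The noncentrality is

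λ = 146 × 0.0726 × 2 / (3(1 − ρ)) = 7.07 / (1 − ρ).

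Three arms by three visits give (3 − 1)(3 − 1) = 4 degrees of freedom, with 5% critical value 9.49.

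| ρ (assumed) | λ | P(joint interaction significant) |
|---|---|---|
| 0.4 | 11.8 | 0.79 |
| 0.5 | 14.1 | 0.87 |
| 0.6 | 17.7 | 0.94 |
| 0.7 | 23.6 | 0.98 |

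**3. Sustained effect.** With 0.33 at both follow-ups, the quadratic form for (1, 1) is 2 − 1 − 1 + 2 = 2, the same as for (1, 0). λ and the probabilities are therefore identical, and the joint test does not distinguish a faded effect from a lasting one.

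**4. Clustering.** The figures in step 2 ignore classes. Take one class per arm in each of 8 schools, hence 146 / 8 = 18.25 completers per class, and a design effect of 1 + 17.25 × ICC. At ρ = 0.6:

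| ICC (assumed) | Design effect | λ | P(significant) |
|---|---|---|---|
| 0.01 | 1.17 | 15.1 | 0.89 |
| 0.02 | 1.35 | 13.1 | 0.84 |
| 0.05 | 1.86 | 9.5 | 0.69 |

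This applies the full design effect to the change scores. A class effect that stays constant over time would cancel from change, and the loss would then be smaller.

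**5. A 3-month contrast.** For one pair of arms, the difference in change from baseline to 3 months has SE = √(4(1 − ρ) / 146). Under the transient scenario it is significant in 5% of trials, the nominal level. Under a sustained d = 0.33, still ignoring clustering, ρ = 0.5 gives SE = 0.117 and power 0.80. At ρ = 0.6 power is 0.88, and at ρ = 0.7 it is 0.95.

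**6. Either follow-up counts.** With no effect at all and each follow-up tested at 5%, the chance of at least one significant result per comparison is 1 − 0.95² = 0.0975 if the two tests are independent. It is 0.091 if they correlate at 0.5, which is the correlation of the two change scores under step 2.

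**The case against.** The strongest reply is that the article does not say what these calculations need. It speaks of an interaction effect, not of a joint or 4-df test, and it does not state how time is coded. With categorical time, a multilevel regression already yields an arm-by-3-month coefficient, which is the contrast wanted here. The dilution of the group effect also depends on coding: under dummy coding with an interaction in the model, the group coefficient is the difference at the reference visit. All of this stands.

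The 3-month effect size and its 95% CI are also planned, so a purely transient effect would show as a 3-month interval around zero. A reader might infer that the plan would necessarily call a 2-week effect a success, or that it has no 3-month analysis. The documents support neither. Nor do the Discussion and Data Analysis contradict each other, since estimating two follow-ups is compatible with ranking one first.

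The scenario is chosen to be unfavourable. The authors say that effects may wane, not that they will, and they schedule booster messages between the two follow-ups.

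Finally, a separate analysis plan could name the contrast. That does not dispose of the point. The article describes its tests and names a primary time point, and it leaves the two unconnected.

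**Conclusion.** The point holds in a limited form. The primary time point is stated only in the Discussion. H1, the primary outcome and the listed tests do not use it, and the planned 3-month estimate is not designated as the test of H1.

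The 79-98% (69-89% with clustering at ρ = 0.6) applies only if a joint interaction test with categorical time is taken alone as the decision on H1. It also rests on assumed correlations and ICCs and on an effect that vanishes completely by 3 months. It shows what the present wording allows, and is not a forecast of what the trial will do. The 9-10% error per comparison applies only if either follow-up may count as success. Over the ranges shown the direction does not change: a joint test rejects far more often than the 5% of a 3-month contrast when nothing remains at 3 months.

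**What to change.** In Data Analysis, and in matching words under Hypotheses and Primary Outcome, state that H1 is tested by the between-arm differences in change from baseline to 3 months: PC-SMILE vs waitlist, C-SMILE vs waitlist, and PC-SMILE vs C-SMILE. Take these as the arm-by-3-month contrasts of the planned multilevel model, with time as a categorical factor. Make the 2-week contrasts secondary. State that neither the group or time main effects nor a joint interaction test alone will be used to declare H1 supported.

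The contrasts should come from the model with baseline as one of the repeated measurements, as Data Analysis appears to intend. Entering baseline as a covariate would be a different model and is not needed for this change.

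The cost is a few sentences. No new data or visits are needed, and once time is coded as categorical the planned model supplies the contrasts.
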